**Methods and analysis:**

We will conduct coordinated randomised controlled trials in six countries to determine if supplementation with indispensable amino acids (IAAs) can improve intestinal barrier dysfunction in six geographically diverse populations of 18–36 months old children with stunting or severe stunting. All trials will measure the same primary outcomes while secondary outcomes will be measured on a per-trial basis using standardised protocols across the project. The primary endpoint will be change in gut permeability as assessed by the lactulose/rhamnose ratio. Secondary endpoints include changes in amino acid and carbohydrate absorption using novel, isotope tracer tests. Other prespecified outcome measures include changes in EE biomarkers and child weight. IAA supplementation will be given daily for 28 days and evaluation of the major endpoints will be at baseline and after 28 days of supplementation.

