### Hypothesis

IAA supplementation will improve biomarkers of gut function and functional measures of carbohydrate and protein absorption among children with stunting and at high risk of EE.

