### Study objectives

The objectives of this study are to determine the effects of IAA supplementation for 28 days on:

The dual sugar LR ratio test.Secondary outcomes, including (1) other biomarkers of EE (plasma intestinal fatty acid binding protein (iFABP), plasma lipopolysaccharide binding protein (LPSBP), faecal myeloperoxidase (MPO) and faecal neopterin (NEO), (2) amino acid digestion, assessed by a DSIT, (3) carbohydrate digestion assessed by ^13^C-SBT and (4) weight gain.

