### Sample size

The sample size for this study is based on the minimum number of participants necessary to observe differences in the primary outcome variable (ΔLR) between intervention and control groups.^47 48^ Each site will contribute data from 60 children, for a total of 360 children across six sites. Assuming an intraclass correlation coefficient (ICC) of 0.1 in ΔLR ratios based on prior reports,^49^ this is sufficient to detect a standardised effect size of 0.40 or greater (a change in ΔLR equal to or greater than 0.4 SD) with an α value of 5% and 80% power. This is equivalent to changes in LR reported in response to other nutritional interventions^47 48^ and is substantially greater than previously reported effect sizes for glutamine and glycine.^50^ A sample size of 60 participants is also sufficient to detect within-site differences with a standardised effect size of 0.84 or greater (ΔLR equal to or greater than 0.84 SD). This difference is on the order of the prior reports of glutamine and glycine supplementation.^50^ Assuming a similar ICC for DSIT results, the same effect sizes (0.40 or greater for pooled analyses and 0.84 or greater for within-site analyses) would be detectable. A prior study on specific amino acid absorption in children within and without EE reported differences in mean amino acid absorption between the group equivalent to an effect size of 0.5.^51^ However, our study will be the first to use the DSIT to evaluate changes in protein digestion associated with a nutritional intervention.

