#### Statistical analysis

To assess the effect of amino acid supplementation on markers of gut function in stunted children, we will first calculate summary values for the LR, ^13^C-SBT and the DSIT. Each of these tests may be summarised in various ways, and so our primary and secondary summary measures for each test are determined a priori. The LR test is the urinary excretion ratio (% of lactulose dose excreted/% of rhamnose dose excreted) over the test period; % lactulose excretion and % rhamnose excretion will be included as secondary outcomes. For the ^13^C-SBT, increases in atom per cent excess over baseline abundance will be converted to percentage of dose recovered (PDR) and curves are fit to the series of breath samples from each participant breath. From these breath curves, the time at which 50% of the final test dose is recovered (T_50_) will be considered as a primary outcome of interest. This choice is based on prior work that demonstrates that T_peak_ and T_50_ are associated with intestinal sucrase activity compared with other aspects of sucrose metabolism (eg, the fraction of the plasma bicarbonate excreted on the breath as opposed to excreted in urine or sequestered).^36^ Other summary measures of the ^13^C-SBT such as cumulative PDR by 90 min may also be influenced by misspecifications of CO_2_ production rate (VCO_2_), which is based on the participant’s estimated body surface area and sex.^52^ The DSIT is summarised as the % digestibility of specific amino acids from spirulina. The method of estimation is summarised in Devi *et al*.^21^ Weight-for-age Z-scores will be calculated based on WHO reference standards.^53^ Plasma concentrations LPSBP and iFABP and faecal concentrations of MPO and NEO will also be analysed.

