For all statistical analysis, p values <0.05 will be considered statistically significant and intention-to-treat analyses will be applied. Both our primary and secondary outcomes will be analysed as change from baseline to endline. Because LR ratios are generally not normally distributed, we will use the non-parametric Wilcoxon rank-sum test to compare the supplementation and control groups within each site. For combined analyses we will use logistic regression models (outcome: LR ratio above vs below EE cut-off, exposure: intervention or control group). For all secondary outcomes, we will similarly use the non-parametric Wilcoxon rank-sum test to compare the supplementation and control groups within each site. For combined analyses we will use linear regression models or logistic regression models based on appropriate cut-off values, including a random effect to account for clustering by site.

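### One p<0.05 rule covers at least nine secondary measures, pooled and site by site, while the outcome tiers conflict and carry no testing rule

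*Protocol article*

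**What the plan says.** All places are in the protocol article.

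- **Threshold.** Statistical analysis: "For all statistical analysis, p values <0.05 will be considered statistically significant". No outcome or level of analysis is exempted.
- **Tests.** Same section: "For all secondary outcomes, we will similarly use the non-parametric Wilcoxon rank-sum test to compare the supplementation and control groups within each site". The next sentence adds combined linear or logistic models with a random effect for site.
- **Which outcomes are secondary.** Study objectives: "Secondary outcomes, including (1) other biomarkers of EE (plasma intestinal fatty acid binding protein (iFABP), plasma lipopolysaccharide binding protein (LPSBP". The list continues with faecal MPO and NEO, amino acid digestion by DSIT, carbohydrate digestion by 13C-SBT, and weight gain. Statistical analysis adds two components of the LR test: "lactulose excretion and % rhamnose excretion will be included as secondary outcomes".
- **A different tiering.** The abstract names the amino acid and carbohydrate absorption tests as secondary endpoints and then says: "Other prespecified outcome measures include changes in EE biomarkers and child weight".
- **Hypothesis.** "IAA supplementation will improve biomarkers of gut function and functional measures of carbohydrate and protein absorption among children with stunting".

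**The concern.** The rule calls a secondary result significant on the same terms as the primary one. It says so for nine or more measures, in the pooled data and again at single sites with 30 children per arm. The stated hypothesis concerns gut biomarkers and absorption measures, which are largely the secondary outcomes. If LR shows nothing, an isolated secondary p<0.05, perhaps from one site, could still be reported as a significant improvement in gut function. The plan as written gives a reader no means of separating such a result from chance.

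The outcome labels do not help. The abstract sets biomarkers and weight apart from the secondary endpoints, while the Study objectives make them secondary. The captions of Figures 3 and 4, which claim to list all primary and secondary biomarkers, include AAT (absent from the Study objectives and Table 2) and omit NEO. No label changes how an outcome is tested.

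**Working it through.** The article states no family-wise error rate, so there is no figure of its own to reproduce.

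**Inputs**
- Level per test: 0.05 (Statistical analysis). The Sample size section says "with an α value of 5% and 80% power" without sidedness. Two-sided is assumed, so 0.025 per test in the favourable direction.
- Secondary measures: iFABP, LPSBP, MPO, NEO, DSIT, 13C-SBT (T50) and weight make 7. Adding % lactulose and % rhamnose excretion makes 9. This is a floor, because the DSIT is summarised per amino acid and the number of amino acids is not given.
- Sites: Table 2 shows that Zambia does neither DSIT nor 13C-SBT, so those two have 5 sites. The other seven are taken as measured at 6. Table 2 has no row for weight, so six sites for weight is an assumption.
- Correlation between outcomes: not given. Range assumed: 0 to 0.8.

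**Number of tests**
- Within site: 7 × 6 + 2 × 5 = 52
- Pooled: 9
- Total: 52 + 9 = 61

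**Expected false positives with no true effect** (does not depend on correlation)
- Either direction: 61 × 0.05 = 3.05
- Favourable: 61 × 0.025 = 1.5

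**Chance of at least one among the nine pooled tests, if independent**
- Either direction: 1 − 0.95^9 = 0.370
- Favourable only: 1 − 0.975^9 = 0.204

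**Allowing for correlation.** Simulation, 100,000 runs, no true effect. For site s and outcome j, z(s,j) = √ρ·c(s) + √(1−ρ)·e(s,j), with c and e independent standard normal. The pooled statistic is the sum of the site values divided by √6 (√5 for DSIT and 13C-SBT). A test is significant when |z| > 1.96.

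| Chance of at least one p<0.05 | ρ = 0 | 0.3 | 0.5 | 0.8 |
|---|---|---|---|---|
| 9 pooled, either direction | 37% | 33% | 27% | 17% |
| 9 pooled, favourable only | 20% | 17% | 14% | 9% |
| All 61, either direction | 94% | 92% | 86% | 67% |
| All 61, favourable only | 75% | 67% | 58% | 41% |

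**Price of formal control.** Bonferroni over nine pooled tests, which is also Holm's strictest step, uses 0.05/9 = 0.0056 per test, with two-sided critical value 2.773. With 180 per arm, a 0.40 SD effect and no ICC adjustment, the expected z is 0.40 × √(180/2) = 3.795, and power is Φ(3.795 − 2.773) = Φ(1.022) ≈ 85%, against 97% at 0.05. For DSIT and 13C-SBT, with five sites and 150 per arm, it is Φ(0.40 × √75 − 2.773) = Φ(0.691) ≈ 76%.

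**The case against.** **The analysis plan may deal with this.** Multiplicity rules for secondary outcomes are commonly left to an analysis plan, and none is shown here. That stands against any complaint that the article omits an adjustment. It does not answer the present point, which is about a sentence the article does contain. A later plan that adjusted the secondary tests would have to depart from the published rule.

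**These are six trials, not one.** The article chose coordinated trials over a single multisite trial and lists a registration entry for each country. Whether one error rate should span six trials and their pooled analysis is debatable. This stands as a caution on the 61-test figures. The nine-test pooled figures do not depend on it.

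**Some structure exists.** There is one primary endpoint, T50 is the lead measure for the 13C-SBT, and additional and optional outcomes are kept separate. A reader might infer that the plan has no hierarchy at all; the article does not support that. What it lacks is a consistent tier list and any testing rule attached to a tier.

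**A chance improvement need not be likely.** A reader might infer that a spurious benefit is probable. On the nine pooled tests, a favourable chance result has probability 9–20%. It exceeds one half only when the site-level tests are counted, and even then not at correlation 0.8 (41%).

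**The hypothesis is not a decision rule.** It joins biomarkers with carbohydrate and protein absorption, and LR is itself treated as a biomarker of EE. Nothing in the article says that one significant secondary result would establish it. The risk lies in how such a result may be reported under the stated threshold.

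**Conclusion.** The concern holds in limited form. The p<0.05 rule covers at least nine secondary measures, each tested pooled and at every site that measures it. The tiers conflict between the abstract and the Study objectives, and none carries a testing rule. With no true effect, the chance of at least one significant pooled secondary result is about 17–37%, against a nominal 5% per test. Across all 61 tests it is about 67–94%, with about three false positives expected.

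These figures rest on assumed correlations of 0 to 0.8, two-sided tests, six sites for weight, and DSIT counted once. More DSIT endpoints would raise the count.

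The single primary endpoint is not affected. The matter deserves correction because it governs what may be claimed from the secondary results.

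**What to change.** 1. In Statistical analysis, limit the p<0.05 significance rule to the primary outcome.
2. State that secondary outcomes are supportive and will be reported as estimates with 95% confidence intervals, without claims of significance. If formal claims are wanted, apply Holm across the pooled secondary comparisons, and first fix which DSIT measures count. A positive LR result should not be a precondition: it would bar formal claims on the isotope tests whenever LR is null, although the article presents those tests as a strength and LR as hard to interpret.
3. Label within-site secondary comparisons descriptive.
4. Use one tier list in the abstract, the Study objectives and Statistical analysis, with biomarkers, weight and the two sugar-excretion measures placed the same way in each. Bring the captions of Figures 3 and 4 into line.

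This is wording only and needs no further data or participants. The cost is that an isolated secondary p value just under 0.05 can no longer be claimed as significant. If Holm is chosen, there is also the loss of power shown in the calculation.

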### Ethics declaration

**Figure 4 F4:**
[figure not shown]
Protocol timeline. This figure shows the complete list of primary (LR) and secondary (DSIT, 13C-SBT, AAT, MPO, LPSBP and iFABP) biomarkers planned across the trials. Not all trials will administer all outcome measures. AAT, alpha-1 antitrypsin; 13C-SBT, 13C sucrose breath test; DSIT, dual stable isotope test; iFABP, intestinal fatty acid binding protein; LPSBP, lipopolysaccharide binding protein; LR, lactulose/rhamnose; MPO, faecal myeloperoxidase.

**Table 1 T1:** A representative total dose of the IAA supplement in milligrams per day, calculated for a 24-month-old child

IAA	Dose
Gly	232.1 mg/day
His	252 mg/day
Ile	453.6 mg/day
Leu	907.2 mg/day
Lys	739.2 mg/day
Met	246.3 mg/day
Cys	123.1 mg/day
Phe	336.0 mg/day
Tyr	336.0 mg/day
Thr	403.2 mg/day
Trp	100.8 mg/day
Val	604.8 mg/day
Total	4734.5 mg/day

Gly is added to support intestinal glutathione synthesis.^54^ The Gly dose is calculated as 63% of AA intake using whole egg protein as a reference.

AA, amino acid; Cys, cysteine; Gly, glycine; His, histidine; IAA, indispensable amino acid; Ile, isoleucine; Leu, leucine; Lys, lysine; Met, methionine; Phe, phenylalanine; Thr, threonine; Trp, tryptophan; Tyr, tyrosine; Val, valine.

**Table 2 T2:** Planned outcome measures in each site

	Ghana	India	Malawi	Morocco	Philippines	Zambia
LR	5-hour	5-hour	5-hour	3-hour	5-hour	3-hour
DSIT	Yes	Yes	Yes	Yes	Yes	No
13C-SBT	Yes	Yes	Yes	Yes	Yes	No
Faecal MPO and NEO	Yes	Yes	Yes	Yes	Yes	Yes
LPSBP and iFABP	Yes	Yes	Yes	Yes	Yes	Yes

13C-SBT, 13C sucrose breath test; DSIT, dual stable isotope test; iFABP, intestinal fatty acid binding protein; LPSBP, lipopolysaccharide binding protein; LR, lactulose/rhamnose; MPO, myeloperoxidase; NEO, neopterin.

Ethical approval for the study has been obtained from the Ethical Review Board overseeing research at each site. The research protocol follows ‘the Standard Protocol Items: Recommendations for Interventional Trials (SPIRIT)’.^25^

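### The pooled analysis of continuous secondary outcomes may be logistic at a cut-off, which fits neither the plan's change-from-baseline rule nor its DSIT power claim in SD units

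*Protocol article*

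**What the plan says.** In the protocol article, the Statistical analysis section sets a common scale for all outcomes: "Both our primary and secondary outcomes will be analysed as change from baseline to endline". Within each site, secondary outcomes are compared by a Wilcoxon rank-sum test. For the combined analysis across sites the plan offers "linear regression models or logistic regression models based on appropriate cut-off values", with a random effect for site. It does not say which outcome takes which model.

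The same section defines the DSIT result as a percentage digestibility, the breath-test result as a time (T50), the plasma and faecal markers as concentrations, and weight as a Z-score. All are continuous. It says that the summary measures are chosen in advance; that statement does not extend to the model.

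The Sample size section carries the LR detectable effects over to the DSIT: "0.40 or greater for pooled analyses and 0.84 or greater for within-site analyses", both in SD units. Table 2 ("Planned outcome measures in each site") shows that Zambia does not perform the DSIT or the breath test.

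**The concern.** Two statements in the article do not fit the logistic option.

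- **Change.** A logistic model of lying above or below a threshold is not, as written, an analysis of change. The pooled LR model in the same section shows the form intended: it classifies the level of the ratio, not its change.
- **Scale.** A detectable effect in SD units describes a difference in means. It says nothing about the power of an odds ratio at a threshold, and the article gives no DSIT threshold.

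The practical stake is power. The plan's own within-site detectable effect (0.84 SD) is larger than the DSIT difference of 0.5 SD that it cites from a prior study, so the pooled analysis must carry the DSIT question. Dichotomising a continuous result weakens that analysis. The trial is also open label, so a model fixed in advance is a useful safeguard.

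**Working it through.** **Inputs from the article.** Significance: "p values <0.05 will be considered statistically significant" (two-sided assumed; the article does not say). Power: "with an α value of 5% and 80% power". Sample: "Each site will contribute data from 60 children, for a total of 360 children across six sites", allocated 1:1. Claim: "this is sufficient to detect a standardised effect size of 0.40 or greater". The DSIT is run at five sites, so at most 5 × 60 = 300 children, 150 per arm.

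**Assumptions.** Normal outcome with SD 1, no losses, site ignored. The cut-offs are mine.

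**1. The plan's own figure.** Detectable effect = (1.960 + 0.842) × √(2/n per arm).
- 180 per arm: 2.802 × √(2/180) = 0.295 SD, against the stated 0.40. Removing site variance with the stated ICC of 0.1 gives 0.280, and dividing the variance by 1 − ICC gives 0.311. Design effects of 1 + 29 × 0.1 = 3.9 and 1 + 59 × 0.1 = 6.9 give 0.583 and 0.776.
- I could not reproduce 0.40 from the stated inputs. That is a separate matter. Below I take 0.40 SD as the effect the plan wants to detect.

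**2. Linear model, DSIT, 150 per arm.** Power = Φ(0.40 × √(150/2) − 1.960) = Φ(1.504) = 93%. With site variance removed (SD √0.9) it is 95%. The detectable effect at 80% power is 0.32 SD.

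**3. Dichotomised, same 150 per arm and same 0.40 SD shift.** Power for two proportions = Φ{[|p1 − p2| − 1.960 × √(2p̄(1 − p̄)/150)] / √([p1(1 − p1) + p2(1 − p2)]/150)}.

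| Cut-off (control distribution) | p1, p2 | Power |
|---|---|---|
| Median | 0.500, 0.345 | 78% |
| 80th percentile (proportion above) | 0.200, 0.329 | 72% |
| 20th percentile (proportion below) | 0.200, 0.107 | 61% |

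For the median: [0.155 − 0.112]/0.0563 = 0.774, and Φ(0.774) = 78%. Simulation (20,000 trials) gave 93.5% for the t-test, 78.4% for the median split, and 72.7% and 60.5% for the two 20/80 splits. The detectable effect at 80% power rises to 0.41 SD at the median and 0.52 SD at the 20th percentile.

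**4. If the stated 80% at 0.40 SD is taken at face value.** A median split keeps 2/π = 0.637 of the information, so power = Φ(2.802 × √0.637 − 1.960) = Φ(0.275) = 61%.

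**5. Choosing the model after seeing results.** In 40,000 simulated null trials with 150 per arm, the linear test alone rejected in 4.9%. Taking the smaller p value of the linear test and one median split rejected in 8.1%.

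**The case against.** The strongest reply is that this is analysis-plan detail. The article condenses a longer protocol, a statistical analysis plan is not shown, and assigning a model and cut-off to each secondary outcome is usual content for it. That stands for the cut-offs: their absence here is not a fault. It does not settle the two mismatches, because the article itself presents a logistic model as an acceptable pooled analysis beside a change-from-baseline rule and an SD-unit claim.

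A second reply is that logistic regression may be meant only where an accepted cut-off exists, which would leave the DSIT linear. The wording permits that reading, and on it nothing is lost: 93% power exceeds the stated 80%. A reader might infer that the plan as it stands discards power. The article does not support that, because no passage assigns the logistic model to the DSIT.

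A third reply is that the size depends on invented cut-offs, and that a median split misses 80% by only about two points. Both are true. The median is the most favourable cut tried.

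A reader might also infer that the model will be picked after the results are seen. The article neither plans nor excludes this. A figure above 8% needs several cut-offs tried per outcome and the smallest p value reported (about 13% for linear plus cuts at 50%, 30% and 20%), a practice the article nowhere describes.

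Finally, the within-site Wilcoxon tests keep the continuous scale whichever pooled model is used. That is so, but they have only 30 children per arm.

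**Conclusion.** The point holds as an internal inconsistency with a conditional cost. The logistic option conflicts with the change-from-baseline rule and with the scale of the DSIT power claim. If it were used for the DSIT, power at 0.40 SD would drop from about 93% to about 78% at a median split and about 60% to 73% at 20/80 splits, below the claimed 80% at every cut tried. If the linear option is used, there is no shortfall. The false-positive rate of about 8% applies only if linear and one median split are compared after the results are known. The figures assume a normal outcome, 150 per arm, no losses, no site effect and cut-offs that the article does not name. These are secondary outcomes, so the change is advisable and does not touch the primary analysis.

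**What to change.** Make the pooled analysis of every continuous secondary outcome a linear model of the endline value on arm and baseline value, with the site effect already planned and a log scale for skewed biomarkers. Report the arm effect as the baseline-adjusted difference. This stays compatible with the change-from-baseline rule: regressing change on arm and baseline gives the same arm coefficient. It is also at least as precise as comparing raw change. With equal baseline and endline variances and correlation r, the residual variance ratio is (1 − r²)/[2(1 − r)] = (1 + r)/2, for example 0.75 at an assumed r of 0.5.

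Keep any logistic analysis as supportive only, with its cut-off fixed before outcome data are analysed by arm. In an open-label trial there is no unblinding date to serve as that limit.

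The cost is a change of wording. Baseline and endline values are already planned for collection, and no sample size or procedure changes.
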